## Background

 Stroke affects 110 000 UK citizens each year at a health and social care cost exceeding £9 billion.^1 2^ National healthcare policy aims to reduce stroke-related disability and its wider impact through targeted primary and secondary prevention.^3^ Before a stroke, many patients experience a Transient Ischaemic Attack (TIA), which is a brief episode of neurological impairment due to a temporary reduction in cerebral blood flow. TIA is associated with a 5% risk of stroke after 7 days and 10% during the next 90 days.^4 5^

Although medical treatments cannot completely eradicate stroke risk, meaningful reductions can be achieved.^6 7^ For example, antiplatelet medication produces an absolute risk decrease between 1.1% to 3.6% according to the agent(s) and population.^8^ Therefore, it is important to promptly and accurately identify TIA so that personalised prevention can be initiated and patients given relevant information, such as temporary restrictions on driving. In the NHS, there is a target for patients with suspected TIA to be reviewed by a specialist hospital service within 24 hours of symptoms being reported to initiate appropriate early treatment including antiplatelet, lipid lowering and/or blood pressure control medication, anticoagulation for atrial fibrillation, and surgical endarterectomy if carotid stenosis is present.^6 9 10^

The incidence of first-ever TIA is approximately 50 per 100 000 people per year;^4 5^ however, there are approximately twice this number of referrals to TIA services because of diagnostic uncertainty.^11^ While many TIAs produce classic movement, sensory, speech and visual impairments lasting <20 minutes on a background of vascular risk factors such as hypertension and diabetes, other conditions can cause transient neurological symptoms. Typically half of the referrals made to TIA services are given a different possible or definite diagnosis following specialist review.^11^

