Currently, therefore, when patients with migrainous symptoms are being reviewed as suspected TIA, individual clinician judgement based on symptom description and previous medical history is frequently used to determine the diagnosis and management. When there is uncertainty about an important diagnosis, a risk-profile approach may be appropriate to guide treatment, but there is currently no risk-score or algorithm to standardise the interpretation of clinical information for suspected TIA patients with migrainous symptoms. Because migraine is common and can present at any age, it often co-exists with other health problems such as hypertension and diabetes, and therefore a simple demographic stratification approach may lead to both large scale under and over treatment depending on whether the individual clinician places more emphasis on the patient’s symptoms or their vascular risk profile.

Further inconsistency in TIA diagnosis and treatment recommendations may also arise because services are provided by hospital specialists with different backgrounds (eg, neurology, geriatric medicine and acute medicine) whereby speciality-dependent training results in differences in exposure to non-TIA conditions. For example, neurologist training and practice includes diagnosis and management of chronic headache, but this is not the case for geriatric or acute medicine. In addition, TIA services are often supported by nurse specialists and trainee doctors, which may further increase variations in diagnosis and treatment. Service pathways also vary, with some involving initial telephone triage before a standard in-person appointment, whilst full remote assessment by phone and video has been accelerated by the COVID-19 response.^21^

This research will address some of the uncertainty for both clinicians and patients faced with migrainous symptoms reviewed as suspected TIA. As it is currently unclear what information is used in diagnostic decision-making, what treatments are offered, and how stroke risk differs according to the specialist diagnosis assigned, data will be collected to describe current practice and report current stroke risk. The information obtained will then be used to characterise high and low stroke risk groups irrespective of the diagnosis assigned and develop a standardised stroke risk assessment. A standardised stroke risk assessment could be used to guide treatment more effectively than clinical judgement alone.

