Patient medical, social and family history	Medical history (migraine/other headaches/hypertension/high cholesterol/atrial fibrillation/diabetes/angina/myocardial infarction/seizures) Current medication (aspirin/clopidogrel/dipyridamole/ticagrelor/warfarin/dabigatran/rivaroxaban/apixaban/edoxaban/other anticoagulant/statin/other cholesterol treatment/blood pressure medication/anxiety or depression medication) Cigarette/E-cigarette smoker Alcohol consumption Caffeine consumption Family history of headaches or migraine Employment status (working/homemaker/unemployed/in education/retired) Computer/screen use (typically every day/most days/sometimes/rarely/never) Driver For females: pre-menopausal/peri-menopausal/post-menopause/receiving hormone treatment
Specialist initiated investigations undertaken/requested	Blood pressure (systolic value/diastolic value) 12 lead ECG Brain imaging (CT/CTA/MRI/MRA/other) Carotid doppler Transthoracic echocardiogram Portable ECG telemetry (eg, Holter or patch) Other investigation
Specialist initiated treatment	Medication started or recommended (aspirin/clopidogrel/dipyridamole/ticagrelor/warfarin/dabigatran/rivaroxaban/apixaban/edoxaban/other anticoagulant/statin/other cholesterol treatment/blood pressure medication/headache or migraine medication) Endarterectomy referral DVLA advice given Headache service referral Neurology service referral Advice given about managing headaches or migraines Other treatment

CTA, computed tomography angiography; MRA, Magnetic Resonance Angiography; TIA, Transient ischaemic attack.

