##### Day 90 data collection

The day 90 data are collected from routine medical records. The information being obtained is summarised in table 2.

**Table 2 T2:** Data collected at day 90

General follow-up from baseline	Results from investigations requested at the study entry TIA clinical review Any diagnosis change between TIA clinical review and day 90 assessment Vital status at day 90 (alive/deceased)
Stroke occurrence	If a stroke(s) has occurred, the following are obtained: Date/time of stroke Stroke symptoms (National Institute of Health Stroke Score) Stroke location (Oxford Community Stroke Project classification) Stroke type (infarction/haemorrhage) Investigations performed with reports (CT/CTA/MRI/MRA/other brain imaging) Treatments received (thrombolysis/thrombectomy/aspirin/clopidogrel/dipyridamole/ticagrelor/warfarin/dabigatran/rivaroxaban/apixaban/edoxaban/other anticoagulant/statin/other cholesterol treatment/blood pressure medication/carotid endarterectomy)
Further TIA and/or migraine symptoms occurrence	If further TIA and/or migraine symptoms have occurred, the following are obtained: Date and time of episode Review by TIA team Review by other service Diagnosis given (TIA/migraine/other) Investigations performed reports (CT/CTA/MRI/MRA/other brain imaging) Treatments received (aspirin/clopidogrel/dipyridamole/ticagrelor/warfarin/dabigatran/rivaroxaban/apixaban/edoxaban/other anticoagulant/statin/other cholesterol treatment/blood pressure medication/treatment for migraine or headaches/carotid endarterectomy) Other neurological events leading to hospital attendance or admission which occurred within the last 90 days
Medication side effects	If new medications were commenced at the study entry TIA clinical review: Free text description of any side effects Medication discontinued

TIA, Transient ischaemic attack.

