### Statistical analysis

#### Cohort description and stroke risk

Data will be presented for the total cohort, specialist clinician more likely diagnosis of migraine group and specialist clinician more likely diagnosis of TIA with migrainous symptoms group. This will include:

Summary descriptive statistics for baseline characteristics, investigations and treatments.Proportions suffering first hospitalisation for stroke by 90 days.Number and timing of stroke events by 90 days (in case of multiple events).Clinical characteristics of stroke events (including clinical and radiological subtype; symptom severity; emergency treatments received).

The proportion of patients experiencing any stroke, defined as at least one clinically documented stroke hospital admission during the next 90 days, will be compared between the specialist clinician more likely diagnosis of migraine group versus the TIA with migrainous symptoms group.

Specialist diagnosis, treatments and 90 day stroke rate across all study patients will also be reported according to:

The professional background of the clinician performing the assessment.The mode of assessment (in person vs remote).Other important service characteristics (eg, referral volume).

Exploratory analyses may also consider:

The clinician confidence rating for their diagnosis (very high/high/uncertain) for migraine or TIA with migrainous symptoms.Patients with single versus multiple stroke events.

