#### Prognostic model and risk assessment tool development

Development of the risk assessment tool will combine information from both Study A and Study B. Using the stages described by Moons *et al*^25 26^ and applying Transparent Reporting of a Multivariable Prediction Model for Individual Prognosis or Diagnosis (TRIPOD) Statement principles,^27^ a prognostic model will be developed through multiple regression to examine the association between clinical characteristics recorded during initial specialist TIA review (including demographics, symptoms and previous medical history) and the 90 day occurrence of any stroke. The initial model will contain all baseline factors independently associated with day 90 stroke and those nominated as plausible by clinicians during Study B initial co-design rounds. Backward stepwise regression will retain variables for the final prognostic model. The performance of the model will be summarised using calibration and discrimination measures. To correct for overfitting and optimism in model performance, an internal validation using bootstrap samples will be performed which splits the data into training and test samples multiple times.

Approaches to visually represent the prognostic model (eg, nomogram)^28^ will be prepared and shared with clinicians during the final round of the study B co-design process to confirm clinical sense and meaning. These will include simple and more complex risk tool options and their matching predictive performance statistics. Options will include clinician preferences about risk assessment tool format identified during the earlier co-design rounds. The final tool preferred by clinicians is expected to reflect a balance between predictive performance and a format/content which is suitable for real world clinical use^29^ e.g. it can be completed within the time restrictions of clinical care with information that is often available, while retaining acceptable utility.

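### The stroke risk model is silent on prevention treatment begun at the same review, so it estimates risk under current selective care although the tool is meant to guide treatment

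*Protocol article*

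**What the plan says.** All references are to the protocol article.

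- **Who decides treatment (Background).** For these patients, "individual clinician judgement based on symptom description and previous medical history is frequently used to determine the diagnosis and management".
- **When treatment begins (Table 1, baseline data).** The baseline form records, under specialist initiated treatment, "Medication started or recommended". The list covers antithrombotic, lipid-lowering, blood pressure and migraine drugs.
- **Whether treatment changes the outcome (Background).** The protocol states that "antiplatelet medication produces an absolute risk decrease between 1.1% to 3.6% according to the agent(s) and population" and that "TIA is associated with a 5% risk of stroke after 7 days and 10% during the next 90 days". The Sample size section accepts that prevention treatment may alter stroke risk in the TIA with migrainous symptoms group, and uses this as one reason for setting a low design rate of 1%.
- **The group comparison (Cohort description and stroke risk).** The proportion with any stroke "will be compared between the specialist clinician more likely diagnosis of migraine group versus the TIA with migrainous symptoms group". Treatments are to be summarised by diagnosis group and service feature. No link between treatment and the stroke comparison is stated.
- **The model (Prognostic model and risk assessment tool development).** It is a regression linking "clinical characteristics recorded during initial specialist TIA review (including demographics, symptoms and previous medical history) and the 90 day occurrence of any stroke". Its starting form takes in every baseline factor independently associated with stroke, plus those nominated by clinicians. Backward stepwise regression then decides what stays.
- **What the tool is for (Background).** "A standardised stroke risk assessment could be used to guide treatment more effectively than clinical judgement alone".
- **Side effects (Table 2, day 90).** These are collected under the condition "If new medications were commenced at the study entry TIA clinical review".

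**The concern.** A model fitted to outcomes that partly reflect treatment predicts risk given the way patients are treated now. If a symptom or risk factor prompts clinicians to start prevention, and prevention works, the fitted association between that feature and stroke is weakened. A clinician using the tool to decide on treatment would naturally take its output as the risk if nothing new were started. The protocol does not say that the output is something else.

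The model text also leaves treatment in an undefined position. The named predictors are demographics, symptoms and history. The selection rule, however, admits any baseline factor associated with stroke, and Table 1 places specialist initiated treatment among the baseline data. Stepwise selection could therefore keep or drop treatment according to the data, and the meaning of the predicted risk would change with it.

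Two smaller matters follow. A small difference in stroke proportions between diagnosis groups could mean that the diagnosis carries little risk information, or that it does and treatment narrowed the gap. And side effects of drugs recommended at the review but begun later may fall outside Table 2's condition, which affects objective 5.

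**Working it through.** **1. The plan's own figures.** For 1% versus 0.015%, 90% power and two-sided 0.05, the continuity-corrected two-proportion formula gives 1287 per group, as stated. Inflation: 2574 / 0.95 = 2709.5 (stated 2709). Events at a 10% TIA-group risk: 0.10 × 1287 = 128.7 (stated at least 128). Events at the design rates: 1287 × 0.01 + 1287 × 0.00015 = 12.87 + 0.19 = 13.06. The point does not rest on an arithmetic error.

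**2. How far treatment lowers the observed risk of a high-risk group.** Observed risk = untreated risk − absolute reduction × share treated. The untreated risk of 10% and the reductions of 1.1 and 3.6 points come from the Background. The protocol gives no baseline risk or time horizon for these reductions, so applying them to 10% at 90 days is an assumption.

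- All treated: 10 − 1.1 = 8.9%; 10 − 3.6 = 6.4%.
- 90% treated: 10 − 0.99 = 9.01%; 10 − 3.24 = 6.76%.

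**3. How far it weakens a predictor.** Assumed: a feature with untreated risk 10% when present and 1% when absent, and 90% versus 10% treated. Observed risk = untreated risk × (1 − share treated × relative reduction). The protocol's figures on a 10% base give relative reductions of 1.1/10 = 11% and 3.6/10 = 36%. The 60% and 80% rows are assumed, to show the range.

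| Relative reduction | Feature present | Feature absent | Risk ratio | Odds ratio |
|---|---|---|---|---|
| none | 10% | 1% | 10 | 11.0 |
| 11% | 9.01% | 0.989% | 9.1 | 9.9 |
| 36% | 6.76% | 0.964% | 7.0 | 7.4 |
| 60% | 4.60% | 0.940% | 4.9 | 5.1 |
| 80% | 2.80% | 0.920% | 3.0 | 3.1 |

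Odds ratio, second row: (0.0901/0.9099) / (0.00989/0.99011) = 9.9. The other rows follow in the same way.

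In a simulation of 400,000 patients under this set-up, adding treatment as a covariate returned odds ratios of 10.4 to 11.8, against a true 11. That recovery holds only because treatment in the simulation depends on nothing but the modelled feature. With real confounding by indication it would be incomplete.

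**4. The group comparison at low rates.** Assumed: untreated risks of 2% and 1%, with 90% and 20% treated, and treatment risk ratios (RR) of 0.8, 0.5 and 0.4.

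- TIA group: 2% × (0.1 + 0.9 RR) = 1.64, 1.10, 0.92%.
- Migraine group: 1% × (0.8 + 0.2 RR) = 0.96, 0.90, 0.88%.
- The true ratio of 2.0 appears as 1.71, 1.22, 1.05.

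This near-null result needs a migraine-group risk of 1%, which is 1/0.015 = 67 times the plan's figure. With 0.015% instead, the true ratio is 2/0.015 = 133. It appears as 1.64/0.0144 = 114 at RR 0.8 and 0.92/0.0132 = 70 at RR 0.4. The gap is reduced but remains very large.

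**5. Tables 1 and 2 side by side.** Table 1 counts a drug as specialist treatment if it was started or only recommended. Table 2 asks about side effects only for drugs commenced at the review. A drug recommended there and begun later by another prescriber meets the first condition but not, on its wording, the second.

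**The case against.** The case against is substantial, and much of it stands.

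- **Treatment is not ignored.** The model text lists demographics, symptoms and history as inclusions, not as a closed set, and its selection rule could admit treatment. Treatment is collected, described by group and acknowledged in the Sample size section. This stands: a reader might infer that the plan shuts treatment out, and the document does not say so. But letting stepwise selection settle the matter does not define which risk is predicted.
- **The unadjusted comparison suits objective 2.** The aim is to describe stroke risk under current practice. Treatment follows from the diagnosis, so adjusting for it answers another question. This stands in full.
- **Treated high-risk patients will look low-risk.** A reader might infer this, but the document's figures do not show it. They take 10% to between 8.9% and 6.4%. Apparent low risk would need a much larger combined effect, such as the assumed 80%, or a lower untreated risk: 4.6% less 3.6 points gives 1%. Setting absolute reductions from other populations against the 1% design rate is not a sound measure either.
- **Treatment shares are unknown.** The Background says it is unclear what treatments are offered. Heavier treatment of the TIA group is plausible, but it is an assumption.
- **A treatment term in the main model, or an untreated prediction, is debatable.** With about 13 events at the design rate and confounding by indication, neither would be reliable as the main result. This stands, and it limits the fix.
- **The detail may be in an analysis plan or a full form not shown.** This is fair for modelling detail, and Table 2 is offered only as a summary. It does not remove the mismatch between the stated purpose and the stated model, since the article leaves open which risk the tool reports.

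**Conclusion.** The point holds as a should-fix. The protocol describes a model whose output is risk under current selective care and a tool intended to guide treatment, and it does not connect the two. For patients whose features prompt treatment, predicted risk will be below untreated risk. On the protocol's own antiplatelet and TIA figures, the fall is from 10% to between 8.9% and 6.4% if all are treated. Under the assumed 90% versus 10% treatment shares, an odds ratio of 11 falls to between 9.9 and 7.4. The direction rests on treatment following the features and being effective, both of which the protocol supports. The size rests on assumed treatment shares and on carrying the antiplatelet effect over to this population.

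The documents do not support saying that high-risk patients would be classed as low-risk, that the comparison by diagnosis is wrong, or that treatment has been excluded from the plan. The comparison would mislead only if a small difference were read as proof that the specialist's diagnosis carries no risk information. The mismatch between Tables 1 and 2 is real but confined to the side-effect item: recommended drugs are already captured as treatment.

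**What to change.** 1. **Prognostic model section.** State that predicted risk is risk under current care, not risk if prevention is withheld, and label the tool accordingly. State that treatment begun at the review is not a candidate for stepwise selection.
2. **Sensitivity model.** Pre-specify one model that adds an indicator, defined in advance, for prevention treatment started or recommended at the review, taken from Table 1. Report how predictor effects and predicted risks change. State beforehand that events may be few (about 13 at the design rates, 128 only if the TIA-group risk is 10%) and that confounding by indication remains.
3. **Group comparison.** Keep the unadjusted comparison as primary. Add, as a descriptive secondary result, stroke proportions in treated and untreated participants within each diagnosis group.
4. **Table 2.** Reword the side-effect condition to cover drugs started or recommended at the review, matching Table 1.

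The labelling needs no data. The sensitivity model and the added proportions use variables already collected, but will be imprecise. The Table 2 change is small but comes partway through enrolment (586 of 2709 participants, 22%, by November 2025), so side effects of recommended drugs may have been recorded differently for earlier participants. That should be stated when objective 5 is reported.

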### Study B: qualitative co-design study

A qualitative co-design study involving two rounds of clinician focus groups and/or individual interviews will be conducted alongside the second half of the prospective cohort study. As well as capturing views from clinicians about the preferred content and format of a risk assessment tool, the Implementation Research Logic Model^30^ will be used as a framework to establish the determinants of implementing the tool into practice, strategies to support implementation, and what indicators could be used to monitor early adoption.

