### Project timeline

Study A commenced participant enrolment in November 2024 and is projected to end in November 2026. Follow-up will subsequently complete in February 2027. The planned start date for study B is November 2026 and end date July 2027.

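### The stated model-building route (entry by association with stroke, then backward stepwise) is likely to overfit, and the bootstrap as described would not by itself correct the tool's coefficients

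*Protocol article*

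**What the plan says.** The section Prognostic model and risk assessment tool development sets out these steps:

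- Entry: "The initial model will contain all baseline factors independently associated with day 90 stroke", together with factors that clinicians nominate in the early rounds of Study B.
- Pruning: "Backward stepwise regression will retain variables for the final prognostic model". No retention threshold is given, and nominated factors are not exempt.
- Performance: "The performance of the model will be summarised using calibration and discrimination measures".
- Safeguard: "To correct for overfitting and optimism in model performance", the plan is that "an internal validation using bootstrap samples will be performed which splits the data into training and test samples multiple times".

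The same section applies TRIPOD principles. It mentions neither shrinkage nor penalisation, and does not say which steps are repeated in each bootstrap sample. The strengths and limitations box and the Discussion both state that there will be no external validation.

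On the timing of clinician input, the Study B section has that work "conducted alongside the second half of the prospective cohort study". The Project timeline has enrolment ending in November 2026 and follow-up in February 2027, and states: "The planned start date for study B is November 2026 and end date July 2027".

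**The concern.** Choosing predictors because they are associated with the outcome in the development data, and then dropping the weaker ones, favours variables whose effects are overestimated by chance. The retained coefficients are too large on average, and predicted risks in new patients are too extreme. The fewer the events per candidate, the worse this becomes.

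Two features of the described safeguard weaken it. A bootstrap draws samples of full size with replacement; dividing the data repeatedly into development and test parts is another procedure, and an analyst could follow either reading. The correction is also aimed at performance. Lowering a reported c-statistic to an honest value leaves the coefficients in a nomogram as they were.

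With no external validation, this internal procedure is the only check before clinicians see the tool. The Study B data collection section expects that a tool with satisfactory performance could be taken up by services quickly.

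**Working it through.** **1. The plan's own figures (Sample size section).** Two-sided 5%, 90% power, 1% against 0.015%: the two-proportion formula gives 1092 per group. With continuity correction it gives 1092/4 × [1 + √(1 + 4/(1092 × 0.00985))]² = 1287 per group, or 2574 in total, as stated. Events for modelling at 10% in the TIA group: 1287 × 0.10 = 128.7, matching the stated minimum of 128. Adding 1287 × 0.00015 = 0.2 for the migraine group gives 128.9.

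**2. Events at the powering rate.** 1287 × 0.01 + 1287 × 0.00015 = 12.9 + 0.2 = 13.1 strokes in the same 2574 people.

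**3. Expected shrinkage before any selection.** Approximation: S = 1/(1 + k/(n × R²)), with n = 2574 and k candidate parameters. R² is assumed to be 15% of its maximum, where maximum R² = 1 − exp{2[φ ln φ + (1−φ) ln(1−φ)]} and φ is the overall event proportion. The article gives no candidate count. Its Table 1 lists dozens of baseline items, so k = 10 to 60 is taken as the range.

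- 10% rate: φ = 0.0501, maximum R² = 0.328, n × R² = 2574 × 0.15 × 0.328 = 126.6.
- 1% rate: φ = 0.0051, maximum R² = 0.0618, n × R² = 2574 × 0.15 × 0.0618 = 23.9.

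| k | Events per parameter, 10% | S, 10% | Events per parameter, 1% | S, 1% |
|---|---|---|---|---|
| 10 | 12.9 | 0.93 | 1.3 | 0.71 |
| 20 | 6.4 | 0.86 | 0.65 | 0.54 |
| 30 | 4.3 | 0.81 | 0.44 | 0.44 |
| 60 | 2.1 | 0.68 | 0.22 | 0.28 |

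**4. Simulation of the stated route, with real signal and no shrinkage.** Assumed: n = 2574; 40 binary candidates, 8 truly predictive; 8 nominated by clinicians (4 of them true); univariable screen at p<0.05, nominated factors added, then backward at p<0.05; 60 runs per scenario, tested on 60,000 new patients. Medians:

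| Events | Apparent c | c in new patients | Calibration slope in new patients |
|---|---|---|---|
| about 129 | 0.71 | 0.67 | 0.77 |
| about 38 | 0.73 | 0.60 | 0.40 |
| about 13 | 0.75 | 0.56 | 0.20 |

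At 13 events, 5 of the 60 runs retained no predictor and are not in the medians. A separate simulation of the same route, also with nominated variables, gave slopes of about 0.63 at 129 events, 0.51 at 64 and 0.21 at 13. A slope of 1 is ideal. A slope of 0.77 means that differences in log-odds between patients are overstated by 1/0.77 = 1.3 times; 0.20 means 1/0.20 = 5 times.

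**5. Does it matter whether selection is inside the bootstrap?** To isolate selection optimism: 43 binary predictors unrelated to stroke (true c = 0.50), screen at p<0.10, backward at p<0.05, 40 replicates × 30 bootstraps. All of these settings are assumptions.

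| Events | Apparent c | Bootstrap of final model only | Bootstrap repeating all selection |
|---|---|---|---|
| 13 | 0.659 | 0.648 | 0.522 |
| 64 | 0.594 | 0.589 | 0.489 |
| 129 | 0.570 | 0.564 | 0.488 |

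At 13 events the final-model bootstrap removes (0.659 − 0.648)/(0.659 − 0.50) = 7% of the optimism; at 129 events, (0.570 − 0.564)/(0.570 − 0.50) = 9%. A repeat with independently written code (40 × 25) gave the same pattern: apparent 0.63, 0.58, 0.57; final model only 0.62, 0.58, 0.57; full procedure 0.48, 0.47, 0.49.

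**The case against.** Four points on the other side deserve weight.

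- **Silence is not a plan.** A reader might infer that the coefficients will never be shrunk, or that the bootstrap starts only after selection. The article says neither. It intends to correct overfitting, cites TRIPOD, and may leave the algorithm to a full protocol or analysis plan that is not shown. A bootstrap that repeats selection fits the text equally well and removes the optimism in step 5. This stands, so the final-model figures there are conditional.
- **The splitting wording may only be loose.** It could describe developing the model in each bootstrap sample and testing on the patients left out. About 37% are left out: some 47 of 129 strokes, but only about 5 of 13. Too few test events is therefore a problem of the low-event case, not of every case.
- **The size rests on assumed inputs.** The candidate count, thresholds and R² are not in the article, and the null simulation has neither signal nor nominated variables. It shows a mechanism and does not forecast this study.
- **Clinician input is not shown to come too late.** A reader might infer this from the November 2026 start. Follow-up runs to February 2027, so round 1 can precede complete outcome data. Round 2 reviews the fitted model and has to come late.

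The article also plans for a tool that performs inadequately. None of this answers the main point: entry by outcome association followed by backward stepwise is stated, and nominated factors are pruned too.

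**Conclusion.** The point holds as a criticism of a stated method. The selection route is likely to overfit, the bootstrap is misdescribed, and a correction of reported performance would not by itself alter the coefficients in the tool. To say that it will certainly produce an overfitted tool goes too far, because the degree depends on events and candidates.

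Under the assumed settings (about 40 candidates, retention at p<0.05, no shrinkage), the calibration slope in new patients is roughly 0.6 to 0.8 at 129 events and about 0.2 at 13. With about 10 candidates and 129 events, expected shrinkage is 0.93 and the problem is small. The 129 events need a 10% stroke rate in the TIA group, and the Sample size section says it is unknown whether that rate applies. If selection is not repeated within the bootstrap, most of the selection optimism remains in the reported figures.

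The two statements on Study B timing do not agree and should be reconciled, but that is a separate and minor matter.

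**What to change.** - **Candidates.** Replace the association screen and backward stepwise with a list fixed from clinical knowledge and Study B round 1 before any predictor-outcome analysis. Limit its length by the observed number of strokes, which can be counted without looking at predictors. At 13 events even 10 parameters are too many (expected shrinkage 0.71).
- **Fitting.** Fit one penalised logistic model, ridge or LASSO. LASSO still selects from the data, but within the penalised fit, and the bootstrap below repeats it. Use Firth only with an intercept correction so that mean predicted risk equals observed risk. In a check with n = 2574 and unrelated binary predictors, plain Firth raised mean predicted risk by about 25% (13 events, 5 predictors), 48% (13 events, 10 predictors) and 4% (129 events, 10 predictors).
- **Validation.** Reword as follows: draw bootstrap samples of full size with replacement, repeat every modelling step in each, test each model on the original data, and subtract the mean optimism from the apparent performance.
- **Tool.** Build the nomogram from the shrunken coefficients.
- **Timing.** Reconcile the Study B section with the Project timeline. Neither date needs to move for the model's sake, provided the round 1 nominations are fixed before the predictor-outcome analysis.

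The cost is wording and computing time. At submission 586 participants were enrolled and Study B had not begun, so the change is still cheap. The downside is that reported performance will look less favourable.
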